### Aims and hypotheses

A randomized, controlled, single-blind trial will be conducted to assess the impact of the ACCOMPAGNE program on the implementation of self-regulatory strategies in the short and long-term in participants with mild to major cognitive disorders. We hypothesize that participants who benefit from the ACCOMPAGNE program will implement more self-regulatory strategies than those who receive conventional recommendations. The implementation of self-regulatory strategies will be assessed 2 and 6 months after the intervention. Because the objective is to investigate the effects of the ACCOMPAGNE program on the implementation of driving strategies, and the link with awareness of driving difficulties, rather than to examine participants' real driving ability, the driving simulator was chosen over on-road testing. This places drivers in a reproducible and controlled driving environment, and will be used to collect objectives as well as subjective measures of driving ability and self-awareness of this ability. For the same reasons, we will use the differences between the points of view of participants and their natural caregivers to measure the changes after the program.

The secondary objectives are to determine the effects of the ACCOMPAGNE program on (a) self-awareness of driving ability, (b) the mood and quality of life of both participant and natural caregiver, and (c) the natural caregiver's burden. We expect that the ACCOMPAGNE program will (a) increase self-awareness of driving ability (b) maintain participants' mood and quality of life despite any changes made, and (c) maintain the mood and quality of life of natural caregivers, and alleviate their burden to a greater degree than conventional care can.

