## Methods/design

### Design

A national randomized, controlled, trial will be conducted. Two-hundred dyads (consisting of participants and natural caregivers) will be randomly assigned either to the ACCOMPAGNE group or to a control group. The trial will take place in four centers in France: memory clinics and geriatric units of the University Hospitals of Lyon, Reims and Tours, and the Geriatric Hospital of Mont d'Or. The effects of the ACCOMPAGNE program will be assessed 2 months and 6 months after the intervention. For 40 participants in the center in Lyon, a test will also be conducted on a driving simulator.

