### Participant timeline

There will be three assessments: a baseline assessment (Time 1), another 2 months after baseline (Time 2) and a third 6 months after baseline (Time 3), as shown in Figure 2. Participants will be randomized between two sequences (i) Baseline (Time 1)>Intervention>Time 2>Time 3 or (ii) Baseline (Time 1) >Control>Time 2>Time 3 (as shown in Figure 2). The intervention will be based on seven collective workshops, spread over three half-days (once a week for three consecutive weeks). For participants recruited by Lyon Hospital, the evaluation will also include a driving simulator test at Baseline (Time 1), Time 2 and Time 3.

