For each task, means and standard deviations of speed, lane position, steering angle, reaction times to traffic lights or unexpected events will be measured. In addition to the objective measures obtained from simulator data, subjective measures will be collected from a questionnaire administered to the participant immediately after each simulator task. While the participant will perform the driving task, the experimenter will fill out the same questionnaire about participant's driving ability (i.e., perception of participant's driving ability). The comparison between the scores obtained from the participant and the experimenter will inform on the participant's driving ability self-awareness. Finally, objective as well as subjective measures will inform on the participant's driving ability and his/her self-awareness of this ability, respectively.

- Mood:

Indicators of mood effects on driving modifications will be measured by the Geriatric Depression Scale 15-item version (GDS 15) (39) in both participants and their natural caregivers at 2 and 6 months.

- Quality of life:

Indicators of quality of life following driving changes will be measured by the Quality of Life in Alzheimer's Disease Scale (QoL-AD) (40) in both participants and their natural caregivers at 2 and 6 months.

-Caregiver burden:

Indicators of caregiver burden following driving changes by the participant will be measured 2 and 6 months by the Zarit Burden Inventory (ZBI) (41) for natural caregivers.

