### Sample size and data analyses

The self-regulation strategy in driving will be considered beneficial if the score of “Self-Regulatory Practice” increases on average by two points (24) 2 months from inclusion. The number of subjects was computed by considering a Student *t*-test for equal variances between the two groups, with a two-sided alpha risk of 5% and a power of 80%. Based on the sample size calculation, 90 participants per group is considered sufficient to detect differences between the two assessments. Because a 10% loss of dyads is expected during the follow-up period, 100 participants per group will have to be recruited, i.e. a total of 200 participants.

Kolmogorov-Smirnov tests will be used to determine the normality of variables. For demographic, clinical, neuropsychological variables, and scores obtained from scales (e.g., the DPPQ), between-group differences will be examined using Fisher's Exact tests, independent Student *t*-tests or Wilcoxon rank-sum tests, as appropriate. The effect size in the intervention group compared to the control group will be quantified by estimating the difference in mean scores between the 2 groups (experimental vs. control) with a 95% confidence interval. A multiple linear regression model will be performed with DPPQ “Current Self-Regulatory Practices” as the dependent variable, and the level of cognitive impairment at inclusion and other characteristics that may have an effect on the outcome criterion as factors. A mixed-effect linear regression model will also be computed with DHQ, GDS-15, Qol-AD and ZBI as dependents variables, and the group (experimental vs. control) and follow-up time (inclusion, 2 and 6 months) as independent variables. The interaction between the intervention group and the follow-up time will be observed.

The concordance between the performance on the driving simulator and the perception of driving ability measured immediately after simulated driving will be estimated by the Lin concordance correlation coefficient and by the Bland & Altman method for continuous criteria, and by the Cohen Kappa coefficient for ordinal criteria. The number of participants who significantly change their estimation at 2 and 6 months compared to before the intervention will be measured from objective and subjective measures at the different points in time.

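### The two stated simulator analyses of self-awareness carry no between-arm contrast, so the simulator sub-study as written does not estimate the programme's effect on self-awareness

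*Protocol article*

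**What the plan says.** All references are to the protocol article.

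- **Objective.** Aims and hypotheses: "The secondary objectives are to determine the effects of the ACCOMPAGNE program on (a) self-awareness of driving ability". The expected direction is also given: "We expect that the ACCOMPAGNE program will (a) increase self-awareness of driving ability".
- **Who is tested, and when.** Design: "For 40 participants in the center in Lyon, a test will also be conducted on a driving simulator". Participant timeline has two randomised sequences, the second being "Baseline (Time 1) >Control>Time 2>Time 3". For Lyon participants "the evaluation will also include a driving simulator test at Baseline (Time 1), Time 2 and Time 3".
- **The simulator measure of self-awareness.** Participant and experimenter complete the same questionnaire about the participant's driving ability. Secondary outcomes: "The comparison between the scores obtained from the participant and the experimenter will inform on the participant's driving ability self-awareness". Table 2 lists simulator measures, with the second part of the DHQ, as indicators of self-awareness.
- **The simulator analyses.** Sample size and data analyses states two. In the first, "The concordance between the performance on the driving simulator and the perception of driving ability" is estimated with Lin's coefficient, Bland-Altman and kappa. The second is a count of participants who significantly "change their estimation at 2 and 6 months compared to before the intervention".
- **The other outcomes.** The same section names the experimental-versus-control comparison for mean scores. It specifies a group-by-time mixed model for DHQ, GDS-15, QoL-AD and ZBI. No simulator variable is on that list.

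**The concern.** The objective asks what the programme does to self-awareness, which is a question about the difference between randomised arms. The design supplies the data for it, since participants are randomised within centres and the Lyon simulator test is repeated at all three visits. The two stated analyses do not use that structure. Concordance describes how well perception agrees with performance in whatever set of people it is computed on. The count describes how many people moved from their own starting point.

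Participants meet the simulator three times over six months and have a cognitive disorder that may progress. Familiarity with the tasks, the passage of time and the course of the disease can each shift self-rating or performance without any workshop. A before-after result cannot tell these apart from the programme, whereas a contrast with the randomised controls can. The simulator is also the only place where self-view is set against a rating by study staff. The second part of the DHQ is scored from the participant's own answers.

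**Working it through.** **1. Does any stated analysis give an arm contrast for simulator self-awareness?**

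| Analysis in the article | Variables named | Arms named? |
|---|---|---|
| Between-group tests; mean difference with 95% CI | Demographic, clinical and neuropsychological variables; scale scores (DPPQ as example) | Yes |
| Multiple linear regression | DPPQ self-regulation subscale | Cognitive level and other characteristics named as factors |
| Mixed model, group by time | DHQ, GDS-15, QoL-AD, ZBI | Yes |
| Lin, Bland-Altman, kappa | Simulator performance and perceived ability | No |
| Number who change | Objective and subjective measures | No; reference is before the intervention |

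The last two rows are the simulator analyses, and neither has a contrast. The reference point of the last also fits the control sequence poorly, since that sequence contains no workshops.

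**2. What a before-after count shows when the programme does nothing.** The article gives no rate of change without intervention, so assume 20% to 40% in both arms.

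- All 40 participants: 40 × 0.20 = 8, and 40 × 0.40 = 16.
- Experimental arm alone, assuming 20: 20 × 0.20 = 4, and 20 × 0.40 = 8.

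Either result could be read as benefit although the arm difference is zero by construction.

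**3. How precise an arm contrast would be.** The split of the 40 is not stated, so assume 1:1, or 20 per arm. The questionnaire's scale and SD are not given either, so assume an SD of the participant-minus-experimenter difference of 1.5 to 2 points. The upper value also follows from rating SDs of 2 with correlation 0.5: √(4 + 4 − 2 × 0.5 × 2 × 2) = 2.

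Unadjusted half-width = 1.96 × SD × √(2/n):

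- n = 20, SD 1.5: 1.96 × 1.5 × 0.316 = 0.93 points.
- n = 20, SD 2: 1.96 × 2 × 0.316 = 1.24 points.
- n = 18 (the article's 10% loss, 20 × 0.9): 1.96 × 1.5 × 0.333 = 0.98 and 1.96 × 2 × 0.333 = 1.31 points.

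Power of a two-sided 5% t-test (noncentral t): with 20 per arm, 34% for a standardised difference of 0.5 and 69% for 0.8; with 18 per arm, 31% and 65%.

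For the proportion of changers, assuming 20% versus 50% with 20 per arm, the half-width is 1.96 × √(0.2 × 0.8/20 + 0.5 × 0.5/20) = 0.28, or 28 percentage points.

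**4. Why the order of averaging matters in the fix.** Suppose a participant overrates by 2 points on three tasks and underrates by 2 on the other three. The mean signed difference is (3 × 2 − 3 × 2)/6 = 0, and its absolute value is also 0. The mean of the absolute differences is (6 × 2)/6 = 2. Only the last registers the poor self-assessment.

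**The case against.** The strongest reply is that this reads silence as a decision. The article condenses a fuller protocol, no analysis plan is shown, and whether a 40-person single-centre sub-study is tabulated by arm is often settled there. Its reference to the time before the intervention may be loose wording for baseline, since the Table 2 title uses similar wording for all participants. The between-group sentence on scale scores is open-ended and could be stretched to the post-task questionnaire.

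Part of this stands. A fuller document may contain the contrast, and the baseline reading is plausible. But the article does not merely omit the simulator analysis. It states both analyses and frames the second as change from a starting point, in a section that names the arms for the other outcomes. The scale-score sentence does not name the simulator questionnaire, and even if stretched would not reach the concordance coefficients or the count.

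Stronger readings that a reader might infer are not supported:

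- **The trial has no randomised estimate for objective (a).** It does. Secondary outcomes makes the second part of the DHQ a self-awareness measure, and the DHQ is in the group-by-time model. Simulator participants complete it too.
- **The arms will be pooled.** The text never says so.
- **The planned methods cannot yield a participant-level outcome.** Bland-Altman rests on participant-level differences, which can be compared by arm.
- **An individual can hardly ever be classed as significantly changed.** The article does not define significant change or give the number of questionnaire items, so no such rate can be derived.

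**Conclusion.** The point holds for the simulator sub-study only. As written, its two self-awareness analyses are agreement and before-after statistics, and they do not estimate the programme's effect, although the design provides for randomised, repeated data that could. That conclusion rests on the text alone.

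The figures only indicate scale. The 8 to 16 spurious changers depend on the assumed 20% to 40% background rate. The half-widths and power depend on an assumed 1:1 split and, for the half-widths, on an assumed SD. An arm contrast would be imprecise, so it is worth stating as an exploratory estimate and cannot serve as a confirmatory test. The primary outcome and the DHQ-based comparison are unaffected.

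**What to change.** Specify the simulator analysis as follows, or confirm that the full plan already does so.

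1. For each simulator participant and visit, take the participant-minus-experimenter questionnaire difference for each task, which is the measure described under Secondary outcomes.
2. Derive two summaries over the six tasks: the mean signed difference (direction of misjudgement) and the mean of the per-task absolute differences (size of misjudgement). Take absolute values before averaging.
3. Compare the arms at 2 and 6 months in a linear model adjusted for the inclusion value. Report the adjusted difference with its 95% CI, labelled exploratory.
4. Keep the concordance coefficients, Bland-Altman results and number of changers, shown by arm and visit, as description only.
5. Replace the reference to before the intervention with the inclusion visit, so that it applies to both sequences.

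The cost is analysis wording; no new data or visits are needed. The downside is the width of the interval, which the report should acknowledge so that a null result is not read as evidence of no effect.

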### Procedure

Participants who are more likely to participate in the study will be identified during attendance at the memory clinics or in the geriatric departments of the four centers. The inclusion criteria will be checked during the pre-inclusion visit. During the visit to determine inclusion, a physician will take the medical history and note any comorbidities (including a diagnosis of cognitive disorder). He/she will also perform a sensory-motor examination using the Short Physical Performance Battery (balance, walking speed, chair raising), the Stop Walking when Talking (motor and verbal double task) and the Handgrip strength to detect physical frailty (Fried's criteria). Socio-demographic data and current medication will also be noted. A nurse will perform a visual examination by assessing the uni and binocular distance visual acuity (Monoyer scale) and near visual acuity (Parinaud scale). He/she will also perform a screening for age-related macular degeneration (Amsler grid), explore the visual field (with a finger) and examine the color perception. A neurocognitive examination will be performed by a neuropsychologist using the Victoria Stroop Test, the Trail Making Test (A and B), verbal fluencies (“P” and “Animals” in 2 min), the Rey Figure copy, and Digit Span and Coding from the WAIS-IV.

On the day of the inclusion visit, the neuropsychologist will administer the DPPQ, DHQ, QoL-AD, GDS-15 scales to the participant. Natural caregivers will respond by themselves to the DPPQ and DHQ scales (based on observations made about the participant's behavior), and to QoL-AD, GDS-15, ZBI. The dyads included in the control group will receive the usual medical recommendations on the same day. The dyads included in the intervention group will be invited to the three half-day workshops. Workshops will start as soon as the experimental group contains four dyads. At 2 and 6 months, the neuropsychologist will administer the DPPQ, DHQ, QoL-AD, GDS-15 scales to the participant. Caregivers will complete the DPPQ and DHQ scales, (based on observations regarding the participant's behavior), and the QoL-AD, GDS-15, ZBI on their own. A questionnaire about life events that took place between each visit will also be administered to the patient and the caregiver at 2 and 6 months. For 40 participants recruited in the Lyon center, observations on a driving simulator will be collected at inclusion, at the 2-month visit and at the 6-month visit.

### Potential pitfalls and unintended effects

This study may face different difficulties. As it tackles the delicate question of driving among olders and more specifically among olders with neurocognitive disorders, we could face difficulties in recruiting participants. Indeed, it is possible that participants with neurocognitive disorders may not take part in this study due to a fear of license loss, even if there is no implication for reporting medically at-risk drivers to the jurisdiction's governing authority. Moreover, we need to include patient/caregiver dyads, thus, in order to be involved in the study, the patient will need to have a natural caregiver, available and willing to participate which reduces the number of potential participants. If recruitment difficulties turn out to be too important, it could lead to a small sample size, which may limit the generalisability of the results. In addition, uncontrolled intercurrent variables related to the individual history of the disease could bias our result. That is why, we choose to control for such variables as best as possible by using questionnaires about life events at 2 and 6 months. Furthermore, the intervention duration (i.e., 3 weeks) may not be sufficient to produce the expected outcomes. Lastly, for the subgroup of patients who undergo a driving task, the use of the driving simulator can generate simulator sickness and may frighten or shock the patient if he/she makes a serious mistake in the driving scenarios such as hitting a pedestrian or another car.

## Discussion/conclusion

For older people with cognitive disorders, driving cessation can lead to a series of negative changes in terms of autonomy and mood for both the patient and the natural caregiver. Recent studies agree on the need to implement interventions to provide support for patients and natural caregivers during the process of adaptation, and then on cessation of driving (14, 15). However, the studies carried out so far have focused on targeted interventions for patients only or natural caregivers only (16, 19, 20), even though interactions between patient and caregiver seem to be at the heart of this process. The onset of cognitive impairment requires the adaptation of driving activity, rather than its abrupt cessation. An intervention program which makes both the patient and the natural caregiver actors in the process of giving up driving seems therefore necessary. This should cover all aspects involved, beginning with an awareness of driving ability, and the subsequent implementation of self-regulated driving strategies, all the way through to complete cessation of driving. This cognitive, social and psychological support should also help to maintain the quality of life and mood of patients and their natural caregivers despite driving limitations. It is also important to consider the environment in which the patient lives. Travel needs and dependence on a car are not the same depending on where the patient lives (e.g., in the countryside or in the city). Severity of disease and the associated road risks will also have to be estimated in any analysis of the maintenance or cessation of driving for these patients. The results will provide information on how to optimize the care of people suffering from neurocognitive pathologies. If the results are conclusive, this approach could be extended to all other centers dealing with this problem.

## Ethics statement

The Regional Ethics Committee (Comité de protection des personnes SUD-OUEST ET OUTRE-MER II) has approved the study (Decision reference number: 20.01612.220050). Authorization for handling these data was granted by the French Data Protection Authority (CNIL: Commission Nationale de l'Informatique et Liberés). The practitioner will give an information document explaining the objectives and the protocol of the study to the patient and the natural caregiver. They will have enough time to think about their participation in the study. Informed written consent will be obtained from all participants before the start of the study.

